##### Quarterly reports of aggregate QI measures

Each organization (*n* = 11) will submit quarterly aggregate reports to the study team on the four quality improvement measures derived from the CDC Guideline for Prescribing Opioids for Chronic Pain: (1) the percentage of patients using long-term opioid therapy who are taking 90 MMEs or more per day, (2) the percentage of patients using long-term opioid therapy who received a prescription for a benzodiazepine, (3) the percentage of patients with a new opioid prescription for chronic pain with documentation that the state Prescription Drug Monitoring Program (PDMP) was checked prior to prescribing, and (4) the percentage of patients with a new opioid prescription for chronic pain with documentation that a urine drug test was performed prior to prescribing. These measures track organization-level opioid prescribing practices and have been recognized as valid measures of opioid management and used in other studies [11, 15, 16].

### Data analysis

#### Analytic plan

Using the complementarity function as described in the taxonomy of mixed methods designs in implementation research [26], quantitative findings will be interpreted in the context of implementation findings for each organization as gathered through qualitative analysis. We will also use a comparative case study approach [27] to compare the similarities and differences across all organizations in the study in their ability to use the 6BBs Clinic Implementation Guide to implement improvements in each of the 6BBs areas and opioid management.

Our analytic plan is guided by our objectives. Objective 1 (implementation) includes an assessment of each organization’s implementation and use of the 6BBs Clinic Implementation Guide and the implementation of improvements using the 6BBs overall. Objective 2 (effectiveness) includes assessment of the effectiveness of 6BBs implementation on processes of care and outcomes.

#### Approach for objective 1 (implementation): to understand adoption and implementation of the 6BBs among participating health care organizations

Objective 1 is to understand the barriers and facilitators to using the 6BBs Clinic Implementation Guide to implement improvements in each of the 6BBs (i.e., leadership and consensus; policies, patient agreements, and workflows; tracking and monitoring patient care; planned, patient-centered visits; caring for complex patients; measuring success). Data to address this aim will come from five main sources: (1) practice documents, (2) orientation and quarterly call notes and email text data, (3) QI lead and staff interviews, and (4) the 6BBs Milestones worksheet.

These qualitative data will be used to understand the barriers and facilitators to implement the 6BBs (see Table 2). These data will be imported into NVivo and coded for themes around barriers and facilitators to implementation of using the 6BBs Clinic Implementation Guide to implement improvements to opioid management. Initial deductive coding will be guided by the CFIR domains, Powell and colleagues’ implementation strategies [28], and each component of the 6BBs. Coding will also be inductively updated through thematic analyses, with a particular focus on staff experiences around using the Clinic Implementation Guide and its utility for facilitating 6BBs uptake, as well as suggested changes to the Clinic Implementation Guide to improve its usefulness related to each component.

Practice documents and the 6BBs Milestones worksheet will be reviewed to determine organizations’ progress on achieving major milestones in each area. Particularly, the proportion of milestones achieved within each area will be compared at the organizational level across the three time points at which those data are collected. Due to the small sample size of participating organizations, data will be analyzed using descriptive statistics of the proportion of milestones reached.

As a supplemental data source, barriers to opioid management indicated on the clinical staff survey will be analyzed and compared from the start to the end of the study. The number and type of barriers and facilitators reported will be summarized descriptively, including mean, median, standard deviations, and change over time both at the organizational level and pooled across all organizations.

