**Methods:**

Data collection is guided by the Consolidated Framework for Implementation Research, Proctor’s taxonomy of implementation outcomes, and the Centers for Disease Control and Prevention’s Guideline for Prescribing Opioids for Chronic Pain. A diverse group of health care organizations with primary care clinics across the USA will participate in the study over 15 months. Qualitative data collection will include semi-structured interviews with stakeholders at each organization at two time points, notes from routine check-in calls, and document review. These data will be used to understand practices’ motivation for participation, history with opioid management efforts, barriers and facilitators to implementation, and implementation progress. Quantitative data collection will consist of a provider and staff survey, an implementation milestones assessment, and quarterly opioid prescribing quality measures. These data will supplement our understanding of implementation progress and will allow us to assess changes over time in providers’ opioid prescribing practices, prescribing self-efficacy, challenges to providing guideline-driven care, and practices’ opioid prescribing quality measures. Qualitative data will be coded and analyzed for emergent themes. Quantitative data will be analyzed using descriptive statistics and clustered multivariate regression.

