#### Approach for objective 2 (effectiveness): to evaluate the effect of 6BBs toolkit implementation on processes of care and intermediate outcomes

We will use quantitative data from the clinical staff survey and quarterly reports of QI measures to assess the effectiveness of 6BBs implementation. The primary effectiveness outcomes from the survey are clinician prescribing practices (e.g., using the PDMP, using a registry to manage patients using long-term opioid therapy, developing a treatment agreement, discussing risks and benefits of opioid therapy with patients, and calculating daily morphine equivalent dosing). Secondary outcomes are clinician prescribing self-efficacy and reported adaptive reserve. Survey data will be exported from Survey Gizmo’s online system and imported into SAS for analysis. We will generate descriptive statistics for survey variables, including mean, median, standard deviation, and plots of distributions for continuous variables, and frequency tables and plots for categorical variables.

Survey responses will be pooled across health care organizations. We expect to receive approximately 450 clinical staff surveys at each of the two time points. A multi-level regression model will be used to determine the association between a pre-post dummy variable and change in each of the three outcomes: clinician prescribing practices, prescribing self-efficacy, and adaptive reserve. The regression model will be adjusted for respondent characteristics captured on the survey, such as clinician type and years of experience. The multi-level model will account for clustering of clinical staffing within health care organizations. A power analysis for a paired-samples *t* test assuming 80% statistical power, significance level of 0.05, and standard deviation of 1 shows the minimum detectable effect is 0.13 from pre to post. Similar or larger effect sizes have been determined for changes in providers’ opioid prescribing knowledge, attitudes, and beliefs, self-efficacy, and opioid management practices following other opioid management QI projects [14, 29].

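### The start-to-end change in survey-reported barriers to opioid management is summarized without adjustment, so it can reflect respondent mix; one more run of the planned multi-level model would address this (low severity)

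*Protocol article*

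**What the plan says.** The Approach for objective 1 opens with: "Objective 1 is to understand the barriers and facilitators to using the 6BBs Clinic Implementation Guide to implement improvements in each of the 6BBs". Its last paragraph turns to the clinical staff survey, which it brings in with the words "As a supplemental data source". The comparison is then stated: "barriers to opioid management indicated on the clinical staff survey will be analyzed and compared from the start to the end of the study". For these responses, counted and sorted by kind, the planned analysis is that they are "summarized descriptively, including mean, median, standard deviations, and change over time both at the organizational level and pooled across all organizations". No covariate adjustment or allowance for clustering is stated for this comparison.

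The Methods part of the abstract names the things whose change over time will be assessed. The list includes "prescribing self-efficacy, challenges to providing guideline-driven care", together with providers' prescribing practices and the quality measures.

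The Approach for objective 2 plans a multi-level regression with a pre-post indicator for "each of the three outcomes: clinician prescribing practices, prescribing self-efficacy, and adaptive reserve". It adjusts for respondent characteristics such as clinician type and years of experience, and it allows for clustering within organizations. Barriers or challenges are not among the modelled outcomes. About 450 surveys are expected at each wave.

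**The concern.** The same survey, given to the same kinds of staff at the same two times, gets two standards of analysis. Prescribing practices, self-efficacy and adaptive reserve get an adjusted, clustered estimate of change. Barriers to opioid management get raw summaries. The plan also goes descriptive for the milestones and the quality measures, but there it gives a reason, the small number of organizations or clinics. That reason does not carry over to a survey with about 450 responses per wave.

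The Clinical staff survey section spans providers, nurses, pharmacists, social workers and medical assistants, as identified by each site's QI lead. The article does not say that respondents will be linked between waves, and its Challenges section foresees a possibly low response rate. If the roles that answer differ between start and end, and roles differ in how many barriers they report, the raw mean moves although nobody's barriers have changed. Medians, types of barrier and organization-level summaries do not remove this.

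Interpretation is also at stake. A fall in barriers to managing opioids could be something the program achieved. Placed under an objective whose opening sentence concerns barriers to using the guide, it needs a sentence saying what it does and does not show.

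**Working it through.** **1. The plan's own survey figure.** Inputs from the Approach for objective 2: paired t test, 80% power, significance level 0.05, SD 1, about 450 surveys per wave. Two-sided testing is assumed, as the article does not state it.

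Minimum detectable effect = (1.960 + 0.842) × 1 / √450 = 2.802 / 21.213 = 0.132. The exact noncentral t calculation also gives 0.132. The stated 0.13 is reproduced. It belongs to a paired test on the modelled outcomes. No test or threshold is set for barriers, so 0.13 serves below only as a yardstick of size.

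**2. Change produced by respondent mix alone.** Let s be the change in one role's share of respondents between waves, and g the difference in mean number of barriers between that role and the rest, in SD units. With no change within any role, the pooled raw mean moves by s × g. The documents give neither s nor g, so both are assumed:

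| Shift in share, s | g = 0.25 SD | g = 0.50 SD | g = 0.75 SD | g = 1.0 SD |
|---|---|---|---|---|
| 5 points | 0.0125 | 0.025 | 0.0375 | 0.05 |
| 10 points | 0.025 | 0.05 | 0.075 | 0.10 |
| 15 points | 0.0375 | 0.075 | 0.1125 | 0.15 |
| 20 points | 0.05 | 0.10 | 0.15 | 0.20 |

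The range is 0.01 to 0.20 SD. Three of the 16 cells exceed 0.13, all with a shift of at least 15 points and a gap of at least 0.75 SD.

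**3. How large a shift can arise by chance.** With 11 organizations, 450 / 11 ≈ 41 respondents per organization per wave, if evenly spread. Four people are then 4 / 41 ≈ 10 points of share. Taking a role share of 50% and independent waves (both assumptions), the standard error of the change in share is:

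- per organization: √(2 × 0.5 × 0.5 / 41) = 0.110, about 11 points;
- pooled: √(2 × 0.5 × 0.5 / 450) = 0.033, about 3.3 points.

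A 10-point shift is therefore ordinary within one organization. Pooled, it is about three standard errors and would need systematic differences in who responds.

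**The case against.** The case against giving this weight is substantial.

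- A reader might infer that the plan contradicts its abstract and drops a promised effectiveness outcome. The documents do not support that. The abstract says that the quantitative data supplement the understanding of implementation progress and show change over time, and a change over time in barriers is planned. Being on the abstract's list does not imply a model either: the quality measures are on it and are also only described. That the abstract's challenges are the survey's barriers is a reasonable reading, not a stated fact.
- A reader might infer that the barriers are put under the wrong objective and will be reported as barriers to using the guide. The plan keeps their own name and calls them supplemental. Objective 1 is also worded more broadly in Study objectives and design and in the Analytic plan, where it covers adoption and implementation of the 6BBs as a whole. Staff-reported barriers to opioid management are plausible context for that.
- A reader might take this to be the only survey measure left unadjusted. That is not established: burnout, engagement and penetration are surveyed too and are not among the three modelled outcomes.
- The article does not say which roles answer the barrier items. If only prescribers do, a shift between prescribers and other staff cannot act, although the mix of clinician types and experience among prescribers still could.
- The size rests wholly on assumed shares and gaps, no test is planned, and the Challenges section already disclaims causal claims.

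All of this stands, and it limits the severity. It does not answer the remaining point. The disclaimer concerns the lack of randomization or a counterfactual, not a change in who responds. Nor is the matter simply left to a fuller analysis plan, since the article itself fixes both the descriptive method for barriers and the list of three modelled outcomes.

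**Conclusion.** The point holds in a limited form. An unadjusted comparison of two waves with no stated linkage can move with respondent mix, and the plan already contains a better method for the same survey. The possible distortion is about 0.01 to 0.20 SD for the pooled mean under assumed share shifts of 5 to 20 points and role gaps of 0.25 to 1.0 SD. It reaches the 0.13 yardstick only where both are large. Shifts of the assumed size arise more readily in organization-level summaries, at about 41 respondents each, than in the pooled one.

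Severity is low. The item is supplemental, no test is planned on it, and no primary or secondary result depends on it. Removing the item from objective 1 would be a preference, not a correction.

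**What to change.** Keep the descriptive summary as supplemental context under objective 1. In addition, estimate the pooled start-to-end change in number of barriers with the multi-level pre-post model and covariates already planned under objective 2. Label it a supplementary or secondary change measure and report it with a 95% CI.

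Add one sentence saying that a fall in these barriers may be an effect of the program and is not by itself evidence about barriers to using the guide.

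The cost is one more run of a planned model and two sentences of text, with no new data. The small downside is one more secondary estimate. The adjustment covers only the respondent characteristics that the survey records, and the organization-level summaries stay unadjusted, so they should be read with respondent mix in mind.

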#### Approach for objective 2 (effectiveness): to evaluate the effect of 6BBs toolkit implementation on processes of care and intermediate outcomes

We will use quantitative data from the clinical staff survey and quarterly reports of QI measures to assess the effectiveness of 6BBs implementation. The primary effectiveness outcomes from the survey are clinician prescribing practices (e.g., using the PDMP, using a registry to manage patients using long-term opioid therapy, developing a treatment agreement, discussing risks and benefits of opioid therapy with patients, and calculating daily morphine equivalent dosing). Secondary outcomes are clinician prescribing self-efficacy and reported adaptive reserve. Survey data will be exported from Survey Gizmo’s online system and imported into SAS for analysis. We will generate descriptive statistics for survey variables, including mean, median, standard deviation, and plots of distributions for continuous variables, and frequency tables and plots for categorical variables.

Survey responses will be pooled across health care organizations. We expect to receive approximately 450 clinical staff surveys at each of the two time points. A multi-level regression model will be used to determine the association between a pre-post dummy variable and change in each of the three outcomes: clinician prescribing practices, prescribing self-efficacy, and adaptive reserve. The regression model will be adjusted for respondent characteristics captured on the survey, such as clinician type and years of experience. The multi-level model will account for clustering of clinical staffing within health care organizations. A power analysis for a paired-samples *t* test assuming 80% statistical power, significance level of 0.05, and standard deviation of 1 shows the minimum detectable effect is 0.13 from pre to post. Similar or larger effect sizes have been determined for changes in providers’ opioid prescribing knowledge, attitudes, and beliefs, self-efficacy, and opioid management practices following other opioid management QI projects [14, 29].

The QI measures we will track as organizational-level outcomes are (1) the percentage of patients using long-term opioid therapy who are taking 90 MMEs or more per day, (2) the percentage of patients using long-term opioid therapy who received a prescription for a benzodiazepine, (3) the percentage of long-term opioid therapy patients with a new opioid prescription for non-cancer chronic pain with documentation that a PDMP was checked prior to prescribing, and (4) the percentage of long-term opioid therapy patients with a new opioid prescription for non-cancer chronic pain with documentation that a urine drug test was performed prior to prescribing. We will report changes in QI measures over time at the clinic level using descriptive statistics due to the small sample size of clinics expected to be enrolled in the study (*n* = 11).

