### Data collection and measures

#### Qualitative data

Qualitative data sources will heavily inform the implementation objective of this study and include staff interviews; notes from orientation and quarterly calls; emails from sites to the study team; completed Clinic Implementation Guide materials; and practice documents, such as policies and workflows. We will use these sources to capture data about organizations’ implementation progress, extent of use of the Clinic Implementation Guide, and barriers and facilitators organizations encounter while using the Clinic Implementation Guide and implementing the 6BBs (see Table 2).

**Table 2 Tab2:** Data sources

Source	Unit of observation	Type	Domains/content	Frequency
Semi-structured staff interviews	QI leads, clinical champions, key staff involved in implementation	Qualitative	Adaptability, complexity, design quality and packaging, execution* Barriers and facilitators to implementation Adoption, acceptability, feasibility, appropriateness, sustainability** Lessons learned	At study startup, midway through, and end
Call notes/emails	Health care organizations	Qualitative	Barriers and facilitators to implementation Adaptability, acceptability, feasibility**	Ongoing
Practice documents	Health care organizations	Qualitative	Intermediate outcomes and care processes (6BBs): Opioid prescribing policies and procedures, clinical workflows, dashboards, patient registries, patient agreements, training and education offerings, opioid tracking and monitoring reports, care plan templates, patient educational materials, screening tools related to opioid management, referral processes between primary care and behavioral health and/or pain specialists	Ongoing
Clinical staff survey	Clinical staff: primary care providers, behavioral health providers, nurses, social workers, medical assistants	Quantitative	Penetration** Engagement in implementation Prescribing self-efficacy (prescribers only) Burnout Adaptive reserve***	At study startup and 12 months later
6BBs Milestones worksheet	Health care organizations	Quantitative	Adoption and fidelity**	At study startup, midway through, and end

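### The 0.13 minimum detectable effect assumes 450 complete pairs; it is not shown to apply to the planned pooled multi-level model, or to the prescriber-only outcome

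*Protocol article*

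**What the plan says.** All of the power material is in the protocol article, under the approach for objective 2 (effectiveness).

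- Expected yield: "We expect to receive approximately 450 clinical staff surveys at each of the two time points".
- Planned analysis: responses are pooled over organizations, and a multi-level regression relates each of three outcomes (prescribing practices, self-efficacy, adaptive reserve) to a pre-post indicator, adjusted for respondent characteristics. "The multi-level model will account for clustering of clinical staffing within health care organizations".
- Power: the calculation is for a different procedure, "A power analysis for a paired-samples *t* test", "assuming 80% statistical power, significance level of 0.05". It concludes that a "standard deviation of 1 shows the minimum detectable effect is 0.13 from pre to post". The next sentence says that earlier opioid-management projects found effects at least about this large.

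Table 2 limits one of the three outcomes: "Prescribing self-efficacy (prescribers only". The section on the clinical staff survey says the same, while listing nurses, pharmacists, social workers and medical assistants among the respondents. There are 11 organizations. The Challenges section warns of a low survey response and of limited ability to detect effectiveness, but leaves 0.13 as it stands.

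**The concern.** The power figure and the planned model appear in one paragraph but rest on different data structures. A paired t test needs each person measured twice. The text gives a count of surveys at each wave and mentions no identifier, no matching and no person-level term in the model. If the two sets of about 450 are partly or wholly different people, the pre-post contrast is less precise than the paired calculation assumes. The number answering the self-efficacy items must also be below 450 unless nearly everyone surveyed prescribes.

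What is at stake is how the survey results are read. The article uses 0.13 as its measure of the survey's sensitivity and sets effects from other projects against it. If the attainable figure is larger for some outcomes, that comparison is too favourable for them.

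**Working it through.** **Inputs from the article:** 80% power, alpha 0.05 (two-sided assumed, as sidedness is not stated), SD 1 (not said whether of the outcome or of the difference), about 450 surveys per wave, 11 organizations.

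**Not given, so assumed over a range:** overlap of respondents between waves, within-person correlation r, share of prescribers, intraclass correlation (ICC), and between-organization SD of change.

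Throughout, K = 1.960 + 0.842 = 2.802.

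**1. The article's figure.** For n pairs with SD of the difference 1, the detectable effect is K/√n = 2.802/√450 = 0.132. The exact noncentral t gives 0.1324. Both round to 0.13, so the figure reproduces. A one-sided test gives 0.117 and does not match. Values that round to 0.13 need between (2.802/0.135)² ≈ 431 and (2.802/0.125)² ≈ 502 pairs. On this basis, nearly every one of the 450 surveys has to belong to a complete pair. If SD 1 is instead the outcome SD, the SD of the difference is √(2(1 − r)), which equals 1 only at r = 0.5.

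**2. Unlinked waves, outcome SD 1.** K√(2/450) = 2.802 × 0.0667 = 0.187, which is 41% above 0.132. Power at 0.13: 0.13/0.0667 = 1.95, and Φ(1.95 − 1.96) ≈ 0.496. For comparison, power at 0.13 with 450 pairs is 0.786. Reaching 80% at 0.13 would take 929 surveys per wave.

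**3. Linked waves, outcome SD 1.**
- Complete pairing, K√(2(1 − r)/450): 0.156 at r = 0.3, 0.132 at 0.5, 0.102 at 0.7.
- 60% overlap (270 pairs, plus 180 unmatched respondents per wave), all respondents used with a person-level term. The variance of the contrast is 2/[270/(1 − r) + 180]. This gives 0.167 at r = 0.3, 0.148 at 0.5, 0.121 at 0.7.

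**4. Prescriber-only outcome, assumed 40 to 50% of 450 (180 to 225 people).**
- Fully paired, SD of the difference 1: 2.802/√225 = 0.187 and 2.802/√180 = 0.209.
- Unlinked, outcome SD 1: 2.802√(2/225) = 0.264 and 2.802√(2/180) = 0.295.
- Fully paired, outcome SD 1, r = 0.7: 2.802√(0.6/225) = 0.145 and 2.802√(0.6/180) = 0.162.

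**5. Clustering in 11 organizations.** With m = 450/11 = 40.9 respondents per organization per wave, the design effect for an unlinked pre-post contrast is 1 − ICC + m × ICC × (1 − c), where c is the correlation of an organization's effect between waves.
- Stable organization effect (c = 1): the organization term cancels. ICC 0.01 to 0.10 gives 0.186 to 0.177, slightly below 0.187.
- Change that differs between organizations (c < 1): for example ICC 0.05 and c = 0.8 gives 0.95 + 40.9 × 0.05 × 0.2 = 1.359, hence 0.187 × √1.359 = 0.218.
- The same feature with 450 complete pairs: variance = τ²Σw² + 1/450, where τ is the SD of change between organizations and w their shares of respondents, with t on 10 df. At an assumed τ = 0.2, the result is 0.24 for equal-sized organizations (Σw² = 1/11) and 0.30 if respondents follow the Table 1 site counts (Σw² = 282/1600 = 0.176). The article states neither τ nor the respondent shares.

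**The case against.** The strongest reply is that nothing is miscalculated. The article names its test and assumptions, and the figure follows from them. That stands, so a reader who inferred an arithmetic error would be wrong.

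Linkage is also under-described rather than ruled out. The word paired, and the fact that links are emailed to staff named by the QI lead, fit repeat contact with the same people, and a condensed article may leave identifiers to the full protocol. With good linkage and high within-person correlation, the detectable effect can match or beat 0.13: 0.121 at 60% overlap and 0.102 with full pairing, both at r = 0.7. A reader might infer that the true detectable effect must be materially larger, say 0.19 to 0.30. The documents do not support that, because the quantities that decide it are not given.

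A reader might also infer that clustering by itself inflates the figure. It does not: every organization contributes to both waves, so a stable organization effect drops out. Only organization-specific change does harm, and its size is unknown. The planned covariate adjustment could recover some precision.

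Finally, the Challenges section concedes limited ability to detect effectiveness and disclaims causal conclusions, and the study's main focus is implementation. Nothing says that a null result will be read as no change. This lowers the stakes but does not make 0.13 the right figure for the planned model.

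What survives is that the stated figure belongs to a procedure the article does not plan to use, and that the prescriber restriction bites even with perfect linkage.

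**Conclusion.** The point holds as a mismatch between the power statement and the planned analysis. The figure of 0.13 is correct for 450 complete, independent pairs with SD of the difference 1. It is not shown to apply to a multi-level model on pooled responses with no stated linkage. It does not apply to self-efficacy on the 450-pair basis unless about 431 or more of the 450 respondents prescribe.

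The size of the discrepancy depends on assumptions:
- unlinked, outcome SD 1: 0.187, with power at 0.13 of about 50%;
- linked, outcome SD 1, r from 0.7 to 0.3: about 0.10 to 0.16 if complete, about 0.12 to 0.17 at 60% overlap;
- prescribers at 40 to 50% of 450: 0.19 to 0.21 fully paired (SD of the difference 1), 0.26 to 0.30 unlinked.

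Any variation in change between organizations adds to these. The documents do not support one replacement number. Nor do they show that the comparison with earlier projects fails, since those effects are not given. This should be fixed, but it does not undermine the study.

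**What to change.** Replace 0.13 with detectable effects computed for the model to be fitted, shown as a sensitivity range. State:

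- whether respondents are linked across waves, and if so whether the model has a person-level term;
- whether SD 1 is the SD of the outcome or of the pre-post difference;
- the assumed overlap and within-person correlation;
- the assumed between-organization SD of change, with 11 organizations;
- a separate line for self-efficacy, using the expected number of prescribers.

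Then compare the earlier projects' effects with the restated figures.

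The cost is a short calculation and one paragraph, with no added participants. The downside is a probably less favourable stated figure. The Project status section says that baseline collection is only starting, so respondent linkage can still be settled if it has not been.
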